## Abstract

**Background:**

Chronic obstructive pulmonary disease (COPD) is a prevalent chronic lung disease, and respiratory muscle dysfunction is one of its key pathogenic mechanisms. Liuzijue, a traditional Chinese health exercise, has been widely applied in COPD rehabilitation, showing benefits in improving pulmonary function and quality of life. However, clinical evidence regarding its specific effects on respiratory muscle function remains insufficient.

**Objective:**

This study describes the protocol of a randomized controlled trial designed to evaluate the effects of Liuzijue exercise on respiratory muscle function and functional outcomes in patients with COPD.

**Methods:**

This study adopts a randomized controlled trial design, with participants randomly assigned to either a control group or a Liuzijue group. The control group receives standardized pharmacological treatment, while the Liuzijue group receives the same pharmacological treatment combined with Liuzijue intervention. The coprimary outcome measures are the 6-minute walk test and surface electromyography of the respiratory muscles. Secondary outcome measures include pulmonary function tests and respiratory questionnaires. Exploratory outcome measures include isokinetic strength testing of the core muscle groups and kinematic analysis.

**Results:**

As of manuscript submission, this trial has received ethical approval (reference number: CHEC2025-149) and secured funding in May 2024. Participant recruitment began on August 1, 2025, and has enrolled 15 participants in the control group and 8 participants in the Liuzijue group to date. Recruitment is expected to be completed by September 2026, followed by data collection until December 2026, with data analysis planned for January 2027 and the final results expected to be prepared and submitted for publication in spring 2027.

**Conclusions:**

This study is one of the first rigorously designed clinical trials to investigate the effects of Liuzijue on improving respiratory muscle function in patients with COPD, aiming to provide reliable clinical evidence for its efficacy in the rehabilitation of respiratory muscle function in this population.

## Introduction

Chronic obstructive pulmonary disease (COPD) is a common, preventable, and treatable yet noncurable heterogeneous lung disease characterized by persistent dysfunction of the airways, alveoli, and pulmonary vasculature, leading to progressively worsening symptoms such as dyspnea, cough, and sputum production [1]. The global burden of COPD continues to rise, largely attributable to heightened exposure to air pollutants and the progressive aging of the population [2]. COPD has become a major contributor to the global disease burden and is currently the third leading cause of death worldwide [3,4]. Epidemiological data indicate that between 1990 and 2019, the growth rates of COPD prevalence and incidence in China were lower than the global average, reflecting notable achievements in COPD prevention and control during this period [5,6]. However, key indicators, including the age-standardized mortality rate, age-standardized incidence rate, and disability-adjusted life years associated with COPD in China, remain at high levels, likely due to accelerated industrialization, urbanization, and population aging. Based on the research conducted by Academician Chen Wang [7], the prevalence of COPD among Chinese adults aged 40 years and older is as high as 13.7%, with an estimated patient population exceeding 100 million. Despite notable progress in prevention and control, COPD remains a major public health challenge in China.

Respiratory muscle dysfunction is a key pathological mechanism contributing to respiratory impairment in patients with COPD. Under the combined influence of multiple pathological factors, including pulmonary hyperinflation, increased ventilatory demand, inflammation, and oxidative stress, the primary respiratory muscles, such as the diaphragm and internal intercostal muscles, are subjected to both abnormal mechanical loading and metabolic imbalance. This sustained pathological burden induces microstructural alterations, including muscle fiber type transformation and mitochondrial dysfunction, ultimately leading to muscle atrophy and reductions in muscle strength and endurance [8,9]. Such alterations not only directly impair the function of the primary respiratory muscles but also indirectly exacerbate dyspnea by diminishing ventilatory reserve capacity. This, in turn, initiates a vicious cycle of worsening dyspnea, activity limitation, and progressive loss of muscle strength, thereby markedly increasing the risk of respiratory failure and systemic sarcopenia [10,11]. A previous study [8] has demonstrated a significant association between respiratory muscle strength and disease progression in COPD. Specifically, in the early stages of the disease (Global Initiative for Chronic Obstructive Lung Disease [GOLD] stages I-II), patients mainly present with respiratory muscle dysfunction, such as weakness of the internal intercostal muscles, while in the advanced stages (GOLD stages III-IV), the function of the primary inspiratory muscles, particularly the diaphragm, becomes significantly impaired [12]. Therefore, improving respiratory muscle function has become one of the key targets in the clinical rehabilitation of patients with COPD.

Clinically, common approaches to improving respiratory muscle function include pharmacological treatment, physical factor therapy, and respiratory muscle strength training. Although evidence from a study [13] demonstrating the benefits of targeted training supports the potential of these approaches to improve respiratory muscle function in COPD, it must be acknowledged that their overall impact is substantially limited by inherent methodological shortcomings. Pharmacological interventions, such as carbonic anhydrase inhibitors, while enhancing respiratory drive, may induce or exacerbate respiratory acidosis [14]. Physical modality therapy requires specialized equipment and professional operation, making clinical applications cumbersome and limiting patient adherence to long-term treatment [15]. Moreover, improper load control during respiratory muscle strength training may lead to adverse events such as headache, coughing, and muscle pain [16]. Therefore, there is a need to explore safer, more effective, and better-tolerated respiratory muscle training programs to further alleviate COPD-related symptoms and improve quality of life. In recent years, traditional Chinese health-preserving exercises have been widely used as nonpharmacological interventions in COPD rehabilitation, including Tai Chi, Baduanjin, Wuqinxi, and Yijinjing, which are notable for their simplicity, safety, and minimal risk of adverse effects [17]. Through a combination of physical movements, breathing regulation, and psychological adjustment, these exercises reflect a holistic rehabilitation concept. Existing studies [18-21] suggest that such exercises not only improve pulmonary ventilation and respiratory muscle strength in patients with stable COPD but also contribute to enhanced quality of life. Consequently, Chinese exercises have become an important adjunctive treatment for patients with stable COPD, offering broad clinical application prospects.

Liuzijue, an important component of traditional Chinese medicine for health preservation and care, is a health-promoting practice that integrates specific breathing techniques, vocalization, and physical movements, and demonstrates characteristics comparable to medical aerobic exercises commonly used in Western rehabilitation medicine, thereby being regarded as a form of aerobic gymnastics. Its technical characteristics involve controlled breathing patterns generated through specific pronunciation, supplemented by coordinated physical movements, aiming to regulate breathing, strengthen the body, harmonize the Qi and the blood, and promote mind-body balance [22,23]. This practice systematically integrates core elements of modern pulmonary rehabilitation, including respiratory muscle training, exercise training, and cardiopulmonary function enhancement [24]. The physical movements of Liuzijue mainly include flexion and extension of the upper limbs, torso rotation, chest expansion, and contraction of abdominal muscle groups. Existing clinical studies [25,26] have demonstrated that Liuzijue significantly improves respiratory function in patients with chronic respiratory diseases, particularly those with stable COPD. Liuzijue effectively alleviates dyspnea, improves lung function, enhances exercise capacity, and ultimately promotes daily functional ability and quality of life in patients through the combination of controlled vocalization and breathing with low-intensity aerobic limb movements. These improvements are typically reflected in increased expiratory volume, improved ventilation efficiency, enhanced exercise endurance, and higher health-related quality of life scores [27-29].

In addition to improving lung function, Liuzijue also exerts a positive effect on skeletal muscle, particularly the function of large muscle groups. Existing studies have shown that Liuzijue, through the pronunciation of the six characters “xu,” “he,” “hu,” “si,” “chui,” and “xi,” can simulate the physiological effects of pursed-lip breathing and diaphragmatic breathing, thereby effectively alleviating dyspnea in patients with COPD [24,30,31]. Moreover, the vocalization process during the practice prolongs exhalation time, which helps improve gas retention. Simultaneously, its coordinated limb movements constitute a low-intensity aerobic exercise model. Through the combined effects of rhythmic limb movement and large muscle group coordination training, it enhances the strength and endurance of major muscle groups such as the quadriceps and biceps [32]. However, despite the demonstrated benefits of Liuzijue in improving respiratory function and enhancing skeletal muscle strength, research on its direct effects on respiratory muscle function remains relatively limited and mostly confined to theoretical discussions. Existing studies [24,30-32] have primarily focused on improving core muscle function, with insufficient clinical evidence regarding its specific impact on respiratory muscle groups such as the diaphragm and intercostal muscles. Nevertheless, Liuzijue still holds potential for improving respiratory muscle function. Its unique combination of breathing control and limb movements may provide effective training stimuli for respiratory muscle groups. However, standardized assessment methods for respiratory muscle strength and biomechanical measurement tools are still limited in this field. In recent years, several studies [33,34] have begun to adopt novel biomechanical analysis techniques, such as isokinetic dynamometers and kinematic analysis, to more accurately quantify muscle movement patterns, providing technical possibilities for the precise evaluation of respiratory muscle function. Nevertheless, the mechanisms by which Liuzijue influences respiratory muscle function remain unclear and require further investigation to establish solid scientific evidence.

Given this background, this study was designed as a randomized controlled clinical trial to systematically evaluate the effects of the traditional Chinese health-preserving practice Liuzijue on respiratory muscle dysfunction in patients with COPD, and to further determine whether improvements in respiratory muscle performance translate into enhanced lung function, thereby fulfilling key objectives of pulmonary rehabilitation in COPD. Additionally, this study assesses the safety of Liuzijue in augmenting overall respiratory efficiency. The anticipated findings are expected to provide practical guidance for the development of clinical pulmonary rehabilitation protocols and offer a theoretical foundation for the application of Liuzijue in the management of respiratory diseases.

## Methods

### Research Design

This study is a randomized controlled clinical trial using a parallel design and evaluator blinding to investigate the effects of Liuzijue on respiratory muscle function in patients with stable COPD. Participants will be recruited from Shanghai Changhai Hospital. All patients will be in a stable phase, either receiving outpatient treatment or following hospitalization. A total of 76 clinically stable patients with COPD will be enrolled in this trial. Before the start of the intervention, respiratory physicians will perform diagnostic assessments to confirm eligibility. Eligible participants will subsequently meet with the research team to receive comprehensive information about this study’s objectives and procedures, and will be given the opportunity to ask questions. Subsequently, participants will sign the informed consent form and will then be randomly assigned to either the control group or the Liuzijue group in a 1:1 ratio.

This trial is conducted in accordance with the 2023 GOLD recommendations [35] and adheres to the diagnostic and evaluation criteria described in *Chronic Obstructive Pulmonary Disease: Diagnosis and Management* [36]. The current trial protocol has been approved (CHEC2025-149) by the Shanghai Changhai Hospital Medical Ethics Committee and has been registered with the Chinese Clinical Trial Registry (ChiCTR2500107043).

The total duration of this study is 9 months. The flowchart of this trial’s design is shown in Figure 1, and the details of patient recruitment, group allocation, interventions, and outcome measures are summarized in Table 1.

**Figure 1. F1:**
[figure not shown]
Flowchart of this trial's design and participant timeline. Eligible patients with stable COPD (GOLD stage II-III) were randomly allocated (1:1) to receive standardized pharmacological treatment alone or combined with a 12-week Liuzijue exercise intervention. Outcomes were assessed at baseline and post intervention, including 6MWT, sEMG, PFT, SGRQ, IKMT, and kinematic analysis. 6MWT: 6-minute walk test; COPD: chronic obstructive pulmonary disease; GOLD: Global Initiative for Chronic Obstructive Lung Disease; IKMT: isokinetic muscle strength test; PFT: pulmonary function test; sEMG: surface electromyography; SGRQ: St. George’s Respiratory Questionnaire.

**Table 1. T1:** Schedule of enrollment, interventions, and assessments according to the SPIRIT^a^ guidelines.

Study period	Baseline	Allocation	Intervention	Assessment
Time point (week)	-2	0	1‐12	13
Enrollment				
Eligibility screen	✓			
Informed consent	✓			
Demographics	✓			
Disease history	✓			
Combination medication	✓			
Centralized guidance	✓			
Phone follow-up	✓	✓	✓	✓
Randomization and allocation		✓		
Interventions				
Control group			✓	
Liuzijue group			✓	
Assessments				
PFT^b^		✓		✓
6MWT^c^		✓		✓
SGRQ^d^		✓		✓
sEMG^e^		✓		✓
IKMT^f^		✓		✓
Kinematics test		✓		✓
Risk management				
Safety assessment			✓	✓
Safety monitoring			✓	✓
Risk prevention			✓	✓
Adverse event reporting			✓	✓

a SPIRIT: Standard Protocol Items: Recommendations for Interventional Trials.

b PFT: pulmonary function test.

c 6MWT: 6-minute walk test.

d SGRQ: St. George’s Respiratory Questionnaire.

e sEMG: surface electromyography.

f IKMT: isokinetic muscle strength test.

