#### Liuzijue Group

Based on the control group, the same standardized medication regimens, as prescribed by clinical respiratory physicians, will be implemented. During this trial, participants will be required to perform regular Liuzijue exercise sessions according to a prescribed regimen. In the two weeks preceding the formal intervention, participants in the Liuzijue group will receive three intensive training sessions conducted by the research team to ensure mastery of the complete movements and key technical elements of the Liuzijue method through systematic instruction. High-definition demonstration videos will be distributed via mobile devices to facilitate correct performance of the prescribed exercises at home, with daily check-ins required. Each participant in the Liuzijue group will be provided with an exercise log card, on which they will record detailed information after each session, including exercise date, time, frequency, duration, location, and perceived exertion (assessed using the Borg CR-10 [Category-Ratio 10] scale, see Table 2). Weekly exercise logs will be submitted at each intensive training session. Simultaneously, researchers will maintain a logbook documenting attendance during the concentrated interventions, collect the exercise log cards, and participants will be engaged in discussions regarding their exercise performance to ensure adherence to this trial’s protocol. During supervised group exercise sessions, trial personnel who have received standardized training will provide on-site correction of participants’ movements. The degree of movement standardization will be systematically documented in the case report forms to ensure consistency of the intervention and to minimize potential impacts on this trial’s outcomes.

**Table 2. T2:** Borg CR-10^a^ rating of perceived exertion scale used to monitor exercise intensity during Liuzijue training sessions. Participants rated their perceived exertion on a scale from 0 ("nothing at all") to 10 ("maximal"), with the target intensity maintained between 4 and 6.

Rating	Description
0	Nothing at all
0.5	Very, very light
1	Very light
2	Light
3	Moderate
4	Somewhat hard
5	Hard
6	Hard
7	Very hard
8	Very hard
9	Very, very hard
10	Maximal

a CR-10: Category-Ratio 10.

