#### IKMT of the Core Muscle Group

IKMT combines the methodological strengths of isometric and isotonic assessments, allowing for precise quantification of muscle strength with excellent reproducibility and reliability [57]. Considering the critical role of core musculature in respiratory assistance, IKMT-based evaluation of core muscle function offers valuable insights into respiratory muscle status. In this trial, an IKANG multijoint muscle training and testing system (NX, A8-3, CHN) will be used to perform isometric assessments of trunk core muscles to examine functional changes induced by intervention. In accordance with established studies [34,58-61], the isometric contraction mode was applied. During testing, participants will be seated in the standardized position recommended by the manufacturer, with the trunk flexion–extension axis aligned at the level of the greater trochanter. The pelvis, lower extremities, and shoulders will be firmly stabilized with fixation devices. Standardized calibration will be performed before testing, and all assessments will be conducted by the same evaluator within a consistent time frame to reduce variability. Each participant will complete three warm-up repetitions followed by five maximal-effort isometric contractions for both trunk flexion and extension. The primary outcome variables include peak torque, peak torque to body weight ratio, time to peak torque, and average power. The IKMT of the core muscle group is illustrated in Figure 4. All measurements will be obtained in week 0 and week 13.

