#### Kinematics Test

The kinematic test uses optical, pressure, and other sensor technologies to quantitatively evaluate the activity of the human musculoskeletal system, thereby elucidating the biomechanical patterns of human movement. In this study, gait analysis and plantar pressure assessment will be conducted in patients with stable COPD to investigate lower limb functional improvements following Liuzijue exercise intervention.

A previous [62] study had demonstrated that gait analysis can sensitively reflect the disease status of patients with COPD and predict their functional prognosis. In this study, a joint motion function testing system (innoMotion, CHN) will be used in combination with a treadmill system (KPOWER, K153D-C-3, CHN) and dedicated gait analysis software (Xmotion, CHN) to evaluate gait characteristics before and after the intervention. The primary outcome measures include joint kinematics of the hip, knee, and ankle, as well as overall gait stability. Before testing, reflective markers will be attached to the participants’ waist, femur, tibia, and foot, after which they will stand on the treadmill. During the test, participants first walk forward at a speed of 3 km/h, and 15 seconds of gait data will be collected; they then walk backward at the same speed, and another 15 seconds of data will be recorded. The gait analysis is illustrated in Figure 5.

Plantar pressure assessment enables accurate evaluation of the medial longitudinal arch and the distribution of plantar forces during walking. Evidence suggests that patients with COPD may present with abnormal plantar pressure patterns, potentially contributing to a decline in quality of life [63]. In this study, a plantar pressure testing platform (Medtrack, CHN) in conjunction with the gait training and testing software (version 5.1.0.8) will be used for analysis. The system is used to record and evaluate the condition of the foot arch and the inversion/eversion curves, thereby assessing changes in plantar pressure before and after the Liuzijue exercise intervention. The plantar pressure testing is illustrated in Figure 6.

Both gait analysis and plantar pressure assessment will be performed in week 0 and week 13.

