### Safety Assessment

A rigorous adverse event monitoring system will be implemented throughout this trial. All adverse events occurring during this study will be recorded in detail, including the time of onset, clinical manifestations, severity, potential causes, and management measures. In the event of an adverse reaction, the clinical investigators will assess the participant’s condition and determine whether continuation in this trial is appropriate. Necessary medical care will be provided, and all serious adverse events will be reported promptly to the Medical Research Ethics Committee of Shanghai Changhai Hospital.

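### Table 1 and the Safety Assessment section disagree on when adverse event collection starts, which leaves the Liuzijue training sessions and the week-0 tests unclear

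*Protocol article*

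**What the plan says.** Table 1 of the protocol article has four columns: baseline (week -2), allocation (week 0), intervention (weeks 1-12) and assessment (week 13). Its risk-management block has rows for safety assessment, "Safety monitoring", risk prevention and "Adverse event reporting". Each is ticked in the last two columns only.

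The Safety Assessment section describes a monitoring system that covers the whole trial and states: "All adverse events occurring during this study will be recorded in detail". It gives no start week and does not say whether the study begins, for this purpose, at consent, at allocation or at week 1.

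Two kinds of activity are placed before week 1:

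- **Training, one arm only.** The Liuzijue Group section says: "In the two weeks preceding the formal intervention, participants in the Liuzijue group will receive three intensive training sessions".
- **Testing, both arms.** The outcome sections place at week 0 a 6-minute walk at the fastest pace the participant can tolerate, a 10 m walk at top speed, "five maximal-effort isometric contractions for both trunk flexion and extension", and treadmill walking at 3 km/h in which "they then walk backward at the same speed". The same tests are repeated at week 13.

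The Randomization and Blinding section has envelopes drawn only after the baseline assessments are complete.

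**The concern.** A schedule table is what staff work from day to day. Read on its own, this one opens the safety window at week 1, after Liuzijue participants have first met the exercise and after everyone has been through one round of physical testing.

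The two exposures have different consequences. Events in training can arise in one arm only, so failing to record them can only lower the Liuzijue count and leaves the control count untouched. Events at the week-0 tests belong to both arms. Losing them does not distort the comparison, but the burden of the test battery would then be recorded at week 13 and not at week 0.

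Safety is one of the trial's stated aims (end of the Introduction, Discussion, Conclusions). There is no independent Data Monitoring Committee, and the monthly audit covers adverse event reporting. An audit needs one defined window to check against. Recruitment has begun, with 23 participants enrolled at submission.

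**Working it through.** The plan gives no figure on this point to reproduce. The check sets the places side by side and then sizes the exposure before week 1.

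**Step 1. When does collection open?**

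| Source | Weeks covered |
|---|---|
| Table 1, all four risk-management rows | 1-12 and 13 |
| Safety Assessment section | whole study, start undefined |

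The blanks at weeks -2 and 0 do not look like a general habit of leaving early columns empty, because the phone follow-up row of the same table is ticked in all four columns. Those calls do not fill the gap. The Control Group section describes that arm's calls as covering medication adherence, activity and general health, and nowhere are calls described as adverse event collection.

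**Step 2. What comes before week 1?**

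- Training: in the two weeks before the formal intervention. The exact timing is unclear. Table 1 puts allocation at week 0 and ticks a centralized guidance row at week -2 only, without saying whether that row is this training. Whether the sessions fall before or after allocation, they precede week 1, and no risk-management row is ticked there.
- Tests: week 0, before allocation, both arms.

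**Step 3. Size of the training exposure.**

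Inputs: 38 participants per group (Sample Size Calculation); 3 training sessions (Liuzijue Group); 2 sessions a day, 5 days a week, 12 weeks, and one supervised hospital day a week (Liuzijue Group).

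- Participant-sessions: 38 x 3 = 114.
- Prescribed sessions per participant: 2 x 5 x 12 = 120.
- Share of all planned sessions: 3 / (3 + 120) = 3/123 = 2.4%.
- Share of supervised occasions, counting one per week: 3 / (3 + 12) = 3/15 = 20%.

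The Liuzijue Group section also speaks of one hospital day plus six home days a week. On seven days the prescription would be 2 x 7 x 12 = 168 sessions and the share 3/171 = 1.8%. The order of magnitude is the same.

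**Step 4. Size of the testing exposure.** There are two rounds, weeks 0 and 13, for all 76 planned participants. Table 1 covers week 13 only, so 1 of 2 rounds (50%) is outside its ticks.

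**Step 5. Range by reading.**

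| Reading | Training sessions uncovered | Test rounds uncovered |
|---|---|---|
| Table 1 governs | 114 of 114 | 1 of 2 |
| Safety Assessment text governs, study starts at allocation | 0 to 114, depending on when training takes place | 1 of 2 |
| Safety Assessment text governs, study starts at consent | 0 | 0 |

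These are exposures, not expected events. The document gives no event rate from which to go further.

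**The case against.** The strongest reply is that the Safety Assessment section is the operative text and the table only a summary. That section promises recording of every event in the study, Ethical Considerations adds reporting of unexpected events to the ethics committee, and the Quality Control section describes trained staff and standard operating procedures at a single hospital. On this view nothing is lost and the table is merely incomplete.

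Much of this stands. A reader might infer from Table 1 that events from the first exposures definitely fall outside the safety window, or that the trial chose to leave them out. The document supports neither. The first is true only if the table overrides the text, and no statement shows such a choice. That staff would open no form for an early event is likewise an inference about conduct.

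A reader might also infer that the week-0 gap flatters Liuzijue. It cannot: those tests precede allocation and are common to both arms. Some data would exist anyway, since oxygen saturation and heart rate are recorded around the 6-minute walk.

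It could be added that an article condenses a fuller protocol, which may define the start of collection. That would excuse silence. It does not excuse a printed schedule that disagrees with the printed safety text. The reply therefore limits the size of the point without removing it.

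**Conclusion.** The point holds as an internal contradiction: the schedule and the safety text give different openings for adverse event collection, and the start is not defined. It does not hold as a demonstrated loss of safety data.

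The size depends on which text staff follow. At most, 114 participant-sessions in the Liuzijue arm (about 2.4% of its planned sessions) and one of two test rounds in both arms are uncovered; at least, nothing is. The upper figure assumes that Table 1 governs, that 38 participants are allocated to Liuzijue and that all attend three sessions. Only the training part could produce one-sided under-recording, and its direction would favour Liuzijue.

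No efficacy outcome, sample size or efficacy analysis is affected. The correction is worth making because it is nearly free, serves a stated aim, and is more useful the earlier in recruitment it is made.

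**What to change.** Reconcile Table 1 with the Safety Assessment section:

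1. In Table 1, extend the ticks for safety monitoring and adverse event reporting to the week -2 and week 0 columns: two rows by two columns, four ticks.
2. In the Safety Assessment section, add one sentence stating that collection runs from the first study procedure after consent and includes the pre-intervention training sessions and the week-0 tests.

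Tabulating events separately for testing, training and weeks 1-13 would help a reader, but it is optional and can be left to the analysis plan.

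The cost is a small amount of extra recording. The Liuzijue safety figures may look slightly less favourable once training events are counted. For participants already enrolled, the trial team should check whether events before week 1 were recorded and say so in the report.
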